### **3.8 Communication with FPs**

We are partnering with the Integrated University Centre for Health and Social Services of West Island of Montreal (IUCHSS). It will be represented by Co-I [name]. We have partnered with 4 Family Medicine Groups (FMGs) in our previous projects and will reach out to them again (in collaboration with [name]) as we prepare to implement this new project.

If patients consent (see Appendix B), family physicians will receive a summary report of their patients' involvement in the study (see Appendix G). The report will include information regarding the presence of specific depression and anxiety symptoms identified from the participant's baseline and follow-up questionnaire, as well as a note on the tools that the patient received as part of the study. These reports will be sent by mail once the participant completes the follow-up questionnaire.

3 weeks after the summary report is sent, we will mail family physicians a brief survey on their impressions on the intervention and reports sent. See survey in Appendix H.

A discussion group will be held with interested family physicians to explore the potential for implementation of self-care interventions in primary care. Information (see Appendix I) will be shared via social media platforms and through e-bulletins of relevant stakeholder organizations, including through the e-bulletin of *Plakett Services Cliniques*, a consulting firm that co-I [name] is working with. The bulletin is sent to over 3000 family physicians in Quebec who have previously been in contact with *Plakett Services Cliniques* for operational support for their practice.

Interested family physicians are invited to provide their contact information via an online form on Simple Survey (see link in Appendix I) so that we may reach them for recruitment. The study coordinator will follow-up with the physicians by phone or email to review the online consent form (see Appendix J).

Consenting physicians will be invited to an online discussion group (separate groups will be offered based on language preference and availability) held via Microsoft teams (MSSS platform). Results of the PanDirect and other similar studies will be presented by members of the research team who will co-moderate the discussion. A draft discussion guide is presented in Appendix K.

### **3.9 Data analysis and statistical power**

Data analysis will be conducted and reported according to CONSORT guidelines. All the quantitative analyses will be carry out with SAS University Edition, STATA 15.0 and R Cran software.

The feasibility of the study will be described using the data collected as part of the study log, recruitment, refusal and uptake rates, completion of surveys, and the rates of missing data will be calculated.

Descriptive analyses will compare characteristics of participants associated with participation and completion of follow-up. Incomplete outcome data will constitute an important aspect of our study. Our general approach will be based on intention-to-treat (ITT) and Inverse Probability Weighting (IPW) will be used to handle missing data. Two sensitivity analyses will be carried out to validate the results obtained by IPW: 1) inclusion of subjects with complete data only; and 2) use of multiple imputation (MI) for missing data. Unless the primary outcome analyses yield different results for completers or MI vs IPW, the secondary analyses will be restricted to completers only.

Baseline imbalance will be assessed by comparing participants randomized to the 2 study arms with respect to 6 pre-specified baseline variables (AGE, SEX, hospital admitted to, COVID-19 DIAGNOSIS, PHQ-9, GAD-7); a maximum of 3 variables with clinically significant differences across arms will be identified.

The comparison of continuous outcomes between intervention and control groups will be based on a simple t-test; linear regression will be used to adjust for baseline imbalance (see above). Similarly, for binary outcome variables (CSQ), Pearson chi-square test and logistic regression will be performed. Effect sizes and 95% confidence intervals (95% CI) will be computed for all the analyses with a continuous outcome, and odds ratio and 95% CI for binary outcomes.

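### The main analysis is meant to be inverse-probability-weighted, but the tests named for it (simple t-test, Pearson chi-square) carry no weights as named and, taken literally, repeat the complete-case sensitivity analysis

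*Protocol*

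**What the plan says.** All of this stands in protocol section 3.9 unless noted.

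- **Main method.** The general approach is intention-to-treat, with IPW to handle missing data.
- **Sensitivity analyses.** "Two sensitivity analyses will be carried out to validate the results obtained by IPW": first "inclusion of subjects with complete data only", second "use of multiple imputation (MI) for missing data".
- **Rule that uses the result.** Secondary analyses are confined to completers unless the completer or MI results for the primary outcome differ from the IPW results.
- **Continuous outcomes.** "The comparison of continuous outcomes between intervention and control groups will be based on a simple t-test". The same sentence then gives linear regression the task of adjusting for baseline imbalance. At most three variables are taken into that adjustment, picked from six according to the differences seen between arms.
- **Binary outcome.** The plan names, "for binary outcome variables (CSQ), Pearson chi-square test and logistic regression", and promises odds ratios with 95% confidence intervals.
- **Size of the problem.** Section 3.2 projects 160 participants. Section 3.4 expects 75% follow-up, that is 120 interviews at 8 weeks.

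Nothing in section 3.9 connects the weights to any of the named tests or models.

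**The concern.** A simple t-test and a Pearson chi-square test, as ordinarily understood, use the observed cases and give each the same weight. On these data that is the complete-case analysis, which the protocol lists as a sensitivity analysis. One procedure would then fill two roles, and the main IPW analysis would not be done.

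This reaches a decision rule. If the result labelled IPW is the unweighted test, the comparison of completers with IPW can never show a difference. Only MI against IPW would still inform the choice of completers for the secondary analyses.

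The other route is to put the weights into these tests with their ordinary variance formulas. Those formulas treat the weights as numbers of patients, or ignore that unequal weights make the estimate more variable. Confidence intervals can then be too narrow. With a quarter of outcomes expected to be missing, the weights matter.

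**Working it through.** **1. Inputs from the protocol.** 160 projected participants (3.2); 75% followed up, 160 × 0.75 = 120 (3.4); 1:1 allocation (3.6); 80% power for a standardised difference of 0.52 with 120 patients, two-sided alpha 0.05 (sample size considerations under 3.9).

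**2. The plan's own figure.** The normal formula for d = 0.52 gives 59 per arm, 118 in total, against 120 stated. With 60 per arm, power is 81.3% by the normal formula and 80.6% by the exact noncentral t, and the smallest detectable d is 0.516. The stated size reproduces. It makes no allowance for weighting.

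**3. Literal reading.** An unweighted two-sample t-test on the 120 observed scores is the complete-case analysis, and so is an unweighted chi-square on the observed CSQ. The difference between completers and IPW is then zero by construction.

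**4. Weights counted as patients, simplest case.** The mean weight is 1/0.75 = 1.33, so 120 completers count as 120 × 1.33 = 160. The standard error is multiplied by √0.75 = 0.866. A nominal 5% test then has error rate 2 × (1 − Φ(1.96 × 0.866)) = 0.0896, about 9.0%. With a constant weight the IPW estimate equals the complete-case estimate, so this figure isolates the effect of miscounting.

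**5. Null simulation with unequal weights.** There were 4000 runs per scenario, with 160 randomised 1:1, 75% followed up on average, and weights from a logistic model on a baseline predictor and arm. *Assumptions, not protocol figures:* outcome-predictor correlation 0.5 (for the binary outcome, on the underlying scale), 75% positive on the binary outcome, and log-odds of follow-up of 0, 0.5, 1.0 or 1.5 per SD of the predictor. The Monte Carlo standard error at 5% is √(0.05 × 0.95/4000) = 0.34 percentage points. Type I error, nominal 5%:

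| Analysis | 0 | 0.5 | 1.0 | 1.5 |
|---|---|---|---|---|
| Mean CV of weights | 0.06 | 0.15 | 0.30 | 0.47 |
| Unweighted t-test, completers | 5.1% | 5.3% | 4.6% | 5.3% |
| t-test, raw weights as counts | 8.4% | 9.7% | 11.7% | 15.0% |
| t-test or weighted regression, normalised weights, model-based SE | 5.1% | 5.8% | 6.6% | 9.6% |
| Chi-square on raw weighted counts | 10.0% | 10.2% | 14.8% | 17.1% |
| Weighted regression on arm, robust (HC3) SE, continuous | 5.0% | 5.1% | 4.5% | 4.3% |
| Same, binary | 5.5% | 4.6% | 5.5% | 4.7% |

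With normalised weights the model-based SE stayed near 0.182, while the empirical SD of the estimate rose from 0.179 to 0.223. The binary robust row is a weighted linear model for the difference in proportions. With arm alone, a weighted logistic model fits the same two weighted proportions.

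**6. Power under valid weighting.** The Kish design effect is 1 + CV², so the effective size per arm is 60/(1 + CV²). For CV 0.06, 0.15, 0.295 and 0.467 this is 59.8, 58.7, 55.2 and 49.3. Power for d = 0.52 is 80.5%, 79.8%, 77.3% and 72.4%, before any gain from adjusting for the baseline score.

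**The case against.** A reader might infer that these tests cannot carry weights at all, so that the main analysis must either collapse into complete cases or report wrong error bars, with 9.0% as the expected error rate. The protocol does not support that. A two-group t-test is a regression on arm, and with weights and a robust variance it kept its level in every scenario above. Section 3.9 lists IPW and complete cases as different analyses, so the charitable reading is that a weighted comparison is intended. It also names linear and logistic regression, both of which accept weights. The 9.0% needs an analyst to count weights as patients, and the protocol says nowhere that this will be done. With normalised weights and mild spread (CV up to 0.15) the error rate was 5.1-5.8%.

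Three further objections carry some force. The weight model and variance estimator are commonly left to the SAP, which is not at hand, so their absence is no finding. This is a pilot trial in which effectiveness is the fourth objective, and the success criteria in section 2 are percentages that no PHQ-9 or GAD-7 p-value decides. And adding baseline score and stratum goes further than the mismatch strictly requires.

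What remains is that the protocol itself fixes test names that do not fit its stated main method. Linear regression is given only the imbalance adjustment, and logistic regression stands beside the chi-square with no link to the weights. A SAP that follows the wording literally would inherit the conflict.

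**Conclusion.** The concern holds in this limited form: the tests named for the main comparison do not carry weights as named. On the literal reading the harm is a main analysis that is not performed and a completers-versus-IPW check without content. It is not wrong error bars, since the unweighted t-test held 4.6-5.3% in the null simulation.

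If weights are added with ordinary variance, error rates can exceed 5%: about 5-10% with normalised weights and 8-17% with raw weights as counts. Both ranges depend on the implementation and on the spread of the weights, and they rest on the assumed dropout strengths and correlation. In these simulations dropout depended on a baseline predictor and not on arm, so they say nothing about bias from differential dropout. No number stated in the protocol is wrong on this point.

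**What to change.** State in section 3.9 that:

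- the main comparison is IPW-weighted linear regression for PHQ-9 and GAD-7 and IPW-weighted logistic regression for CSQ, with robust (sandwich) or bootstrap standard errors, the bootstrap refitting the weight model in each sample;
- each model contains arm and the symptom stratum used in randomisation (section 3.6) and, for the two scales, the baseline score already collected (section 3.4), all fixed in advance in place of covariates chosen by the imbalance observed;
- the unweighted t-test and chi-square serve only the complete-case sensitivity analysis.

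The odds ratio for CSQ then becomes conditional on stratum, and the text should say so.

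The cost is wording and code. No new data are needed, and the SAS, Stata and R already named are sufficient. Weighting may lower power as shown in step 6, but that is the price of using IPW at all, and baseline adjustment may recover some of it.

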#### **3.2 Sample and exclusion criteria**

We have already assembled a cohort of 267 patients 65+ years old for a previous study (PCAP study, see SMRC protocol #18-04). Among these, 80% (n=213) agreed to be contacted again for future research opportunities. These patients were discharged home following hospitalization between October 2018 and December 2019 at the medical or geriatric units of two general hospitals on the west island of Montreal. Among the original cohort, 40% were born outside Canada; 30% received homecare services, and 65% were high-risk for functional decline, death, and increased health care service utilization.

With anticipated 75% participation, we project a sample size of 160. Exclusion criteria for the current study will comprise: moderate to severe cognitive impairment (using BOMC a brief cognitive screen); unable to read in English or French (self-reported); hearing impairment (as judged by research staff); currently receiving counseling or psychological therapy (as these treatments may conflict with the self-care interventions); currently living in a long term care or other medicalized facility, or presenting suicidal intent (as identified through the final item of the PHQ-9 which will be asked at screening). Patients with suicidal intent will be contacted by the coach supervisor for further assessment and referral (see section 3.7 below). Patients receiving antidepressant or anxiolytic medications will be eligible for the study, as will all patients who do not meet the threshold for clinically-significant symptoms of depression and/or anxiety as they

may still benefit from the intervention Participants who begin counseling or psychological therapy after enrolment will not be withdrawn. Participants who are not eligible or interested in the study will be invited to contact 2-1-1 to follow-up on any needs (see [www.211qc.ca/en/](http://www.211qc.ca/en/)).

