### **3.4 Data collection from patient participants**

Following consent, RAs will conduct the baseline interview (see Appendix C) with participants. Measures to be collected are as follows:

- Symptoms of depression: We will use the PHQ-9, a widely used 9-item measure of depression severity to determine presence and type of depressive symptoms. The PHQ-9 was selected based on its wide use in medical populations, established severity ranges and sensitivity to change, validation as a screening measure, and inclusion of somatic symptoms which are recognized as a core domain of depression, not confounding diagnosis in patients with chronic disease. The criterion for clinically-significant depression is 10 (but as specified above, this is not being used as an eligibility cut-point).
- Severity of anxiety symptoms: The seven item GAD-7 will be used as a continuous measure of severity of anxiety symptoms (internal consistency: Cronbach  $\alpha = .92$ ; test-retest reliability: intraclass correlation=0.83). Scores range from 0-21. The criterion for clinically-significant anxiety is 10 (also not used as an eligibility cut-point)
- Alcohol abuse: The 4 item CAGE questionnaire with a score ranging from 0-4 will be used to detect alcohol abuse and dependence. Although a cut point of 2 or more is used conventionally (average sensitivity 0.71, specificity 0.90), the cut point of 1 or more results in greater sensitivity as expected, and has been used in some studies. We will categorize as: no, possible (score of 1), or probable (score of 2+).

- Other baseline data: include questions on hospitalizations and ED visits during the previous 6 months, COVID diagnoses in patient or family, current living arrangement, having a family caregiver, and current homecare services.

At 8 weeks, with an anticipated follow-up rate of 75% (120 end of project interviews), the PHQ-9, and GAD-7 will be re-administered, along with enquiry into use of the self-care materials, perceived helpfulness in managing mental health problems, satisfaction with the intervention, and use of health services including any counseling or therapy started, during the 8-week study period. Satisfaction will be measured with a 3-item version of the Client Satisfaction Questionnaire (CSQ-3), highly correlated with the CSQ-8 ( $r=0.94$ ).

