### **3.7 Follow-up of at risk participants**

All research staff members who have patient contact are trained to follow-up on any reported suicidal thoughts to identify if there is intent to act. All patients who report only thoughts, but no intent, will be given the telephone numbers of local crisis/suicide hotlines. The coach supervisor will follow-up immediately with any participant who divulges suicidal intent. If the patient is deemed at risk, the patient's most responsible physician (as identified by the participant at that time) will be informed with the patient's consent. Furthermore, if the coach supervisor identifies any immediate risk of self-harm, the patient will be directed to the nearest emergency room, will

be given the telephone numbers of a suicide hotline and the most responsible physician will be informed (the police will be alerted if the patient with suicidal behaviours refuses to go to the emergency room). Those with suicidal intent identified at screening will be excluded from the study; those with suicidal intent during follow-up will be withdrawn from the study.

Participants with a PHQ-9 score of 20 or more will be encouraged to see their physician. If patients consent, the identified physician will be informed.

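### Agreement of the completers and MI analyses with IPW cannot detect loss that depends on the unseen 8-week score, yet it is called validation and decides that secondary analyses use completers only

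*Protocol*

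**What the plan says.** Protocol section 3.9 takes an intention-to-treat approach and handles missing data by IPW. It then says: "Two sensitivity analyses will be carried out to validate the results obtained by IPW". The first is "inclusion of subjects with complete data only"; the second is "use of multiple imputation (MI) for missing data". Neither comes with a stated departure from missing at random.

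The outcome of the comparison is then used as a rule: "Unless the primary outcome analyses yield different results for completers or MI vs IPW, the secondary analyses will be restricted to completers only".

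Three other places bear on this:

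- Section 3.2 projects the enrolled number: "With anticipated 75% participation, we project a sample size of 160". Section 3.4 plans the 8-week interview "with an anticipated follow-up rate of 75% (120 end of project interviews". PHQ-9 and GAD-7 are scheduled at baseline and 8 weeks only.
- Section 3.7 states that "those with suicidal intent during follow-up will be withdrawn from the study". Suicidal intent at screening is already an exclusion, so these withdrawals reflect change after baseline.
- Section 3.5 gives up to three coach calls to one arm only. The coaches are trained to follow up on suicidal thoughts.

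**The concern.** A sensitivity analysis supports a result only against the assumption it relaxes. IPW is valid if, given the variables in the weight model, loss does not depend on the unseen outcome. MI in its standard form needs the same, given the variables in the imputation model. An unadjusted completers t-test generally needs loss within each arm to be unrelated to the outcome, which is stronger. None of the three relaxes the assumption most open to doubt: that people who miss the 8-week interview score as their observed data would predict.

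Two things are at stake. First, agreement would be reported as validation of the PHQ-9 and GAD-7 comparisons. Second, the same agreement would move the secondary analyses to completers only, which rests on the strongest assumption of the three.

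**Working it through.** **Inputs from the protocol.** 160 enrolled and 120 followed up (sections 3.2 and 3.4); detectable effect 0.52 SD with 80% power, two-sided alpha 0.05, equal groups (section 3.9).

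**Inputs assumed.** The outcome SD (4, 5 or 6 points), and delta, the amount by which missing participants score worse than the analysis assumes. The protocol gives neither.

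**1. The plan's own figures.** 213 × 0.75 = 159.75, about 160; 160 × 0.75 = 120, or 60 per arm. Power at 0.52 SD with 60 per arm is 80.6% by t-test (81.3% by normal approximation). The stated figures reproduce.

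**2. Shift in the contrast.** An arm mean is wrong by (missing share) × delta. With 25% missing per arm:

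- Coached arm only affected: the effect is overstated by 0.25 × delta. Tools-only arm only affected: it is understated by the same amount.
- Same delta and same missing share in both arms: 0.25 × delta − 0.25 × delta = 0.
- Same delta, but 30% and 20% missing: (0.30 − 0.20) × delta = 0.10 × delta.

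| Delta, coached arm only (SD) | Shift (SD) | What remains of 0.52 |
|---|---|---|
| 0.2 | 0.05 | 0.47 |
| 0.3 | 0.075 | 0.445 |
| 0.5 | 0.125 | 0.395 |
| 0.8 | 0.20 | 0.32 |
| 1.0 | 0.25 | 0.27 |

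**3. Tipping point for an observed 0.52 SD.** The standard error is √(2/60) = 0.183 SD, so significance needs 1.96 × 0.183 = 0.358 SD. The margin is 0.52 − 0.358 = 0.162 SD, and 0.162 / 0.25 = 0.65 SD. In points this is 2.6, 3.2 or 3.9 at SD 4, 5 or 6. The standard error is held fixed for simplicity.

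**4. How widespread the pattern must be.** About 80 are randomised per arm and 20 are missing. The margin equals 0.162 × 80 = 13 SD summed over the arm's missing participants: all 20 worse by 0.65 SD, or 10 worse by 1.3 SD and the rest as assumed.

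**5. Do the three methods agree when the assumption fails?** We simulated 2000 trials of 160 with a true difference of 0, a baseline–outcome correlation of 0.5 (assumed) and about 25% missing in each arm. Loss rose with the unseen 8-week score in the coached arm and was unrelated to it in the other. IPW and MI used arm, baseline score and their interaction; this is the simulation's choice, since the protocol lists no variables.

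| Analysis | Mean estimate (SD) |
|---|---|
| Full data | −0.003 |
| Completers | −0.213 |
| IPW | −0.166 |
| MI | −0.165 |

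The mean absolute gap within a trial was 0.017 SD between MI and IPW, and 0.054 SD between completers and IPW. The sampling SD of the estimates was about 0.17. The gaps are small against that noise, and all three methods share a spurious benefit of coaching.

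**The case against.** **The SAP may add a departure from missing at random.** It may, and MI can be run with shifts. But the protocol itself names the two analyses, states their purpose and hangs a rule on their agreement. That rule is a decision taken here, not a detail left open.

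**The two analyses have value.** This stands. MI against IPW checks the weight and imputation models. Completers against IPW shows whether observed factors drive loss; in the simulation they did move apart somewhat. Section 3.9 also plans to describe who completes follow-up. A reader might infer that the checks are worthless; they are not. They answer a different question.

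**Nothing shows that loss will be informative or differ by arm.** This also stands. The protocol gives no expected number of withdrawals for suicidal intent, and step 4 suggests that a few alone would not overturn an effect of 0.52 SD. That low mood leads people to miss the interview is plausible but undocumented. Nor does the protocol say that all three analyses use the same covariates; the six variables in section 3.9 are for judging baseline imbalance.

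**This is a pilot.** Three of the four objectives are feasibility or acceptability, and the success criteria set no efficacy threshold. That limits the weight of the point. But the fourth objective is effectiveness at 8 weeks, and the sample size section is argued on power for PHQ-9 and GAD-7.

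**Conclusion.** The point holds in a limited form. Agreement among IPW, MI and completers cannot show that the result is robust to loss that depends on the unseen score, so it should not be called validation or used to move secondary analyses to completers.

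With 25% missing, a departure of about 0.65 SD across all missing participants in the coached arm, and none in the other, would cost an observed effect of 0.52 SD its significance. Smaller departures, up to 0.5 SD in the table, would not. These figures rest on assumed deltas and SDs.

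A reader might go further and infer that the coaching effect will be biased, or that it will be overstated. The documents do not support that. Bias in the contrast requires informative loss that differs by arm in amount or kind, and it could run in either direction. Coach contact in one arm and withdrawal for suicidal intent make such a difference possible; they do not establish it.

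**What to change.** - Keep IPW and MI.
- Add a delta-adjusted MI (tipping-point) analysis for PHQ-9 and GAD-7 with arm-specific shifts: coached arm only, tools-only arm only, and unequal shifts in both. Report the delta at which the conclusion changes. Equal shifts alone would say little, since they nearly cancel when loss is similar.
- Describe the completers and MI analyses as checks under missing at random (stronger for completers), not as validation of IPW.
- Delete the rule that agreement restricts secondary analyses to completers. Use IPW or MI for them, as for the primary outcomes.

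The cost is about a day of programming on the MI already planned. No extra data are needed and no clinical rule changes. The price is that results may have to be described as less robust.

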### **3.6 Randomization**

Participants will be randomized to Group 1 (tools only) or Group 2 (tools with coaching) by a computer-generated randomization schedule that uses random block sizes, with an allocation ratio of 1:1; SAS University Edition will be used. In order to ensure allocation concealment, the study coordinator will first verify eligibility and informed consent. Subsequently, the unique patient identifier (PID) from the recruitment log will be entered into the randomization schedule, along with: date of consent, date of baseline interview. An automated interface will then assign the participant to the study group. Participants will be stratified based on whether their symptoms are none to mild or moderate to severe to ensure an equal balance of symptom severity in both study groups. Participants will be categorized as none to mild if their PHQ-9 is less than 10 and their GAD-7 score is less than 10. Participants with a PHQ-9 score of 10 or more and/or a GAD-7 score of 10 or more will be categorized as being in the moderate to severe group.

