#### Sample size considerations:

For continuous outcomes (PHQ-9, and GAD-7), a total sample size of n=120 patients will allow us enough power (80%) to detect at least a moderate Cohen's effect size (0.52) between the 2 intervention groups (group equal size, 2-tailed test and alpha 0.05). For the binary outcomes CSQ (75%+) with the same sample size and power, a minimum difference between the two study groups of 20-26% can be detected

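### The planned t-test never adjusts for the randomisation stratum and adjusts for baseline PHQ-9 or GAD-7 only if they look imbalanced, so free precision is given up and the test is mildly conservative

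*Protocol*

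**What the plan says.** Section 3.6 randomises 1:1 in blocks of random size and stratifies: "Participants will be stratified based on whether their symptoms are none to mild or moderate to severe". The lower stratum is defined as "none to mild if their PHQ-9 is less than 10 and their GAD-7 score is less than 10", and everyone else falls in the upper one. The stratum is therefore a function of the two baseline scores.

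Section 3.4 measures PHQ-9 and GAD-7 at baseline and again at 8 weeks.

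Section 3.9 says that the comparison of continuous outcomes "will be based on a simple t-test; linear regression will be used to adjust for baseline imbalance (see above". The cross-reference is to a step that compares the arms on "6 pre-specified baseline variables (AGE, SEX, hospital admitted to, COVID-19 DIAGNOSIS, PHQ-9, GAD-7" and then states that "a maximum of 3 variables with clinically significant differences across arms will be identified". Both baseline scores are candidates and the stratum is not. The section does not define a clinically significant difference, and it does not say whether the t-test or the regression is the headline result.

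The sample size text in section 3.9 assumes an unadjusted comparison with 120 patients ("group equal size, 2-tailed test and alpha 0.05"), an effect size of 0.52 and 80% power.

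**The concern.** The baseline value of the same scale is usually the best available predictor of the follow-up value. Here it is measured on everyone, and a coarse version of it drives the randomisation. The plan uses it in the analysis only when the arms happen to differ on it, and stratification is there to make that less likely.

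Three things are at stake:

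- **Precision.** The recontact cohort is fixed at 213, and 213 × 0.75 ≈ 160 enrolled, 160 × 0.75 = 120 followed up. Precision cannot be bought with more patients.
- **Calibration.** A t-test that ignores a prognostic stratification factor overstates its standard error.
- **Pre-specification.** The covariates in the regression depend on an unstated judgement made after the arms have been compared.

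**Working it through.** **1. The plan's own figure.** Inputs from section 3.9: d = 0.52, 60 per arm, two-sided alpha 0.05.

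- Normal approximation: n per arm = 2(1.960 + 0.842)² / 0.52² = 58.1, rounded up to 59, or 118 in total.
- Power with 60 per arm: Φ(0.52 × √(60/2) − 1.960) = Φ(0.888) = 0.813. With the noncentral t it is 0.806, and the minimum detectable effect is 0.516.

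The stated 120, 80% and 0.52 reproduce.

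**2. Adjusting for baseline score.** If the baseline-to-8-week correlation is r, ANCOVA reduces the residual SD by the factor √(1 − r²). The protocol gives no r, so a range is assumed. The formulas of step 1 (t-based) then give:

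| r (assumed) | √(1 − r²) | Power at d = 0.52 | Detectable effect (SD) | Total N for 80% power |
|---|---|---|---|---|
| t-test | 1 | 0.806 | 0.516 | 120 |
| 0.3 | 0.954 | 0.842 | 0.492 | 108 |
| 0.5 | 0.866 | 0.904 | 0.447 | 90 |
| 0.7 | 0.714 | 0.977 | 0.368 | 62 |

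Confidence intervals narrow by the same factor: about 5%, 13% and 29%.

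**3. Calibration of the t-test.** Stratified randomisation removes most of the between-stratum variation from the difference in means, but the t-test's standard error still contains it. If the stratum explained a share R² of outcome variance and balance were perfect, the real type I error would be 2[1 − Φ(1.96/√(1 − R²))]. With R² = 0.10 as an illustration this is 2[1 − Φ(2.066)] = 0.039.

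A simulation followed the protocol's design: 160 randomised in blocks within the two-scale stratum and 120 random completers. Assumed were block sizes of 2, 4 and 6 and a PHQ-9/GAD-7 correlation of 0.7. With 10,000 null trials (Monte Carlo standard error about 0.002) the results at nominal 0.05 were:

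- t-test: 0.044, 0.040 and 0.032 at r = 0.3, 0.5 and 0.7. A repeat with 20% to 35% in the upper stratum gave about 0.032 to 0.049 over r = 0.7 to 0.3.
- ANCOVA in every trial: 0.046 to 0.052.
- Adjusting only when imbalance is seen: 0.042 to 0.044 at r = 0.3 and 0.020 to 0.032 at r = 0.7, depending on the threshold.

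**4. How often the baseline score would be adjusted for.** This depends on the missing threshold. The table gives the chance that baseline PHQ-9 differs between arms by more than the threshold among 160 randomised. The unstratified column uses a standard error of √(4/160) = 0.158 SD and a normal approximation.

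| Threshold (SD) | Stratified (simulated) | Unstratified |
|---|---|---|
| 0.10 | about 40% | 53% |
| 0.20 | 8–11% | 21% |
| 0.25 | 3–5% | 11% |
| 0.30 | 1–2% | 6% |

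The simulated figures are for 20% to 35% in the upper stratum. Widening that to 15% to 47% gives 35–44%, 7–12%, 2–6% and 1–2%. At 0.2 SD, at least one of the two scores exceeds the threshold in 13–21% of trials.

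**The case against.** The case for leaving the text alone has real substance.

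- **The promised power is delivered.** A reader might infer that the trial is underpowered. It is not: the t-test gives 0.806 at the stated effect, and about 81% to 83% in simulation under stratification. The loss exists only relative to ANCOVA, and at r = 0.3 it is about 4 points.
- **The error is in the safe direction.** A reader might infer inflated false positives. The t-test is unbiased and its type I error is at or below nominal. Inflation, to about 0.056 to 0.066, appears only if the smaller of the two p-values could be chosen, and the protocol does not say that it will be. The shortfall is also modest, because the two-scale stratum and 25% attrition both loosen the stratum's hold on each outcome.
- **The baseline scores are candidates.** A reader might infer that they will almost never be adjusted for. That holds exactly for the stratum. For the scores it depends on a threshold the protocol does not state.
- **Discretion is bounded.** There are six named variables and at most three are selected, on clinical grounds.
- **It is a pilot.** Three of the four objectives, and all the success criteria in section 2, concern feasibility or acceptability.
- **The SAP may name the headline model.** That omission alone would be no finding.

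All of this limits the size of the point. It does not remove it. Section 3.9 fixes the t-test and the imbalance trigger itself, so this is not a detail left open. Effectiveness at 8 weeks is objective 4 and is formally powered.

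**Conclusion.** The point holds as one of efficiency and pre-specification. It should be fixed, but it does not threaten the validity of the trial. The stratum is never adjusted for. Whether the baseline score is adjusted for turns on an undefined judgement, and the chance for PHQ-9 runs from about 40% of trials to 1–2% as the threshold moves from 0.1 to 0.3 SD. The t-test's real type I error is about 3% to 5%, lower as the correlation rises. Power forgone at d = 0.52 is about 4, 10 and 17 points at correlations of 0.3, 0.5 and 0.7.

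The correlation, the share in the upper stratum, the block sizes, the correlation between the two scales and random missingness are all assumptions, because the protocol states none of them. The direction was the same at every correlation tried.

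**What to change.** In section 3.9:

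- Make the main analysis of each scale a linear regression of the 8-week score on arm, the same scale's baseline score and the randomisation stratum, whatever imbalance is observed.
- Remove the step that selects up to three covariates from observed differences. Keep the baseline comparison as description only.
- Report the t-test as a supportive, unadjusted result.
- The logistic regression for CSQ is tied to the same selection step, so name its covariates in advance when that step is removed.

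The inverse probability weights already planned for missing data can be applied to this regression. The cost is a few sentences in the protocol and matching text in any SAP. All covariates are already collected, and no patients, visits or data items are added. The sample size can stay as it is, with the gain taken as precision.
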